**Figure 2. f2:**
[figure not shown]
Flowchart referral aid

Patients who agree to participate in the study will be counseled in accordance with the referral aid. First, the PN inquires about earlier cessation attempts and smoking cessation methods patients may have used during these attempts. Second, the PN informs the patient about the available EBSCIs and their advantages and disadvantages based on the information provided in the intervention’s manual. If necessary, the manual also allows PNs to provide information on possible reimbursements by health insurers. Third, the PN and patient discuss which EBSCI best fits the patient’s needs and preferences. Fourth, the smoker selects an EBSCI and chooses a cessation date. Lastly, depending on the EBSCI chosen by the patient, PNs schedule at least one follow-up appointment in two–five weeks, in order to evaluate and, if necessary, to select another EBSCI.

If the smoker is not (yet) interested in participating, PNs are advised to give the smoker a flyer to take home. This flyer contains information about participating in the study and a summary of the different EBSCIs. This way, smokers may be stimulated to consider smoking cessation at a later point in time. If the smoker is uncertain about participating, PNs are advised to, in addition to handing out the aforementioned flyer, schedule a follow-up meeting or telephone call with the smoker for further discussion on participation in the study.

### Intervention materials

Materials will consist of a small (letterbox-sized) package, which will be sent via post and a website (www.stopwijzer.nu). Taking into account the potential of low health literacy of patients, the materials have been written in a clear and comprehensible language in accordance with the applicable Dutch guidelines (Language level B1) (Ministerie van Algemene Zaken, 2019). The main component is an instruction manual for using the referral aid. This manual consists of the following elements (see also Figure 3):1.an introduction, which explains the goals and relevance of the intervention and gives a brief overview of the different EBSCIs and the other elements of the referral aid;2.instructions in using the referral aid, which include a roadmap of the most important steps and a summary in the form of a flowchart;3.an overview of possible reimbursements of EBSCI’s by health insurers with a calculation tool to help patients provide insight into how much money they can save by quitting smoking;4.an overview of the different EBSCIs, in the following order: face-to-face counseling, eHealth, counseling via telephone, group counseling, nicotine replacement therapy, pharmacotherapy, and nonevidence-based ‘cessation’ methods (acupuncture (White *et al.*, 2014), laser therapy (Kerr *et al.*, 2008), auriculotherapy (Bier *et al.*, 2002), hypnoses (Carmody *et al.*, 2008), and e-cigarettes (Kalkhoran and Glantz, 2016);5.guidelines for following up the initial consultation;6.some concluding remarks and room for taking notes.

**Figure 3. f3:**
[figure not shown]
Brief overview of content interventions’ manual

#### Flowchart handout

Two of the elements of the instruction manual, a summary of the referral aid and a summary of health insurer’s reimbursements policies, are printed on A5 carton handouts in order to be used by PNs as a quick reminder (see also Figure 4).

**Figure 4. f4:**
[figure not shown]
Flowchart handout

#### Placemat

PNs also receive a decision matrix printed on a plastic desk pad. The desk pad can be used as a reminder for the PN or as a conversation tool during a consultation with a smoking patient (see also Figure 5). The matrix lists the EBSCIs mentioned above and gives an outline of their target groups, strengths, and weaknesses, effectiveness, and costs. The matrix can also be accessed via the project’s website.

**Figure 5. f5:**
[figure not shown]
Decision matrix, provided in the form of a desk pad and available online

#### Flyers

PNs will receive flyers describing 1) a summary of information on EBSCIs, 2) a list of the contact information of the research team and 3) a link to the project’s website.

#### Promotion materials

In addition, the package also will contain a stack of business cards with the contact information of the research team and a link to the project’s website. Also enclosed will be a poster, which is used to promote the project in the practice’s waiting room. A digital version of the poster that can be displayed on waiting room screens will be sent via email. Lastly, a pen and a notebook featuring the project’s logo will be included as a small reminder.

#### Website

The project’s website will consist of a general part and a password-protected part. PNs from both the experimental and the control conditions will be able to register new patients in the password-protected part. PNs from the experimental condition can furthermore access digital copies of the manual and other materials (e.g., the placemat, handouts, and flyer). Patients from the experimental condition can access materials delivering the same information as they receive from their PN. PNs and patients from the experimental condition can access a frequently asked questions (FAQ) page tailored to their needs. Smokers from the control condition can only access the general part of the website, which will contain general information about the project and the study

### Prompts to promote intervention use and to prevent questionnaire attrition

PNs will be sent a newsletter once a month in order to keep them informed of the progress of the study and to remind them of their participation. PNs who lag in recruitment will be approached personally via telephone call or practice visit. Further, PNs will be sent personal postcards during the holiday season or when they have recruited their fifth participant. Participants will be able to contact the research team via the project’s website or via email or telephone.

Additionally, to the questionnaires we sent directly to the patients, we also sent out paper questionnaires to the general practices, to be delivered to patients by the PN, which intend to reduce attrition in the period between the initial meeting and receiving the questionnaire via post or email. Smokers can complete these paper questionnaires directly after their meeting with a PN, for example, in the practice’s waiting room. Pre-addressed envelopes including postage are provided with all paper questionnaires.

### Usability testing

A prototype version of the intervention was tested by five HCPs in order to identify any ambiguities within the intervention. Open interviews were held in which the HCPs reviewed the materials together with the primary researcher and the HCPs’ comments and opinions were used as input for the final intervention. Most changes were minor and related to terminology, for example, using the term HCP instead of PN in materials to not exclude other possible participants. Other comments focused more on design elements such as making a more distinct distinction between EBSCIs and nonevidence-based interventions using visual techniques.

## Data collection

### Measures

#### Tobacco abstinence

The primary outcome of the study will be 7-day point prevalence abstinence (PPA) measured at 6-month follow-up from baseline (Mudde *et al.*, 2006; Cheung *et al.*, 2017a). Secondary outcomes are 24-hour PPA and 3-month prolonged abstinence (Mudde *et al.*, 2006). Assessing 6-month prolonged abstinence is not possible due to the study design, since follow-up measurement will take place six months after answering the baseline questionnaire irrespective of the date the participant quit smoking. Prolonged abstinence will be assessed by asking patients whether they have refrained from smoking tobacco since their last quit attempt allowing for a two-week grace period during which the participant could smoke one–five cigarettes. Furthermore, patients will be asked whether and how often they have tried to quit smoking (i.e., no cigarette for 24 h) during the intervention period. If patients indicate to smoke at follow-up, they will also be asked how many cigarettes on average they smoke per day. Because of minimal personal contact with the research staff and reduced possible contact with HCPs because of COVID-19, biochemical validation will not be possible. Therefore, all tobacco abstinence measures will be assessed at 6-month follow-up using self-report with an added ‘bogus pipeline’ question (‘Do you object if we come to do a saliva test to check your smoking status?) to reduce socially desirable responses by including the threat of biochemical testing (Aguinis *et al.*, 1993, Adams *et al.*, 2008). Previous studies suggest that the difference between self-reported abstinence rates and those verified with biochemical validation is negligible (Glasgow *et al.*, 1993; Patrick *et al.*, 1994; Velicer and Prochaska, 2004). The number of cigarettes smoked on average per day will be measured at baseline as well.

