### Potential limitations

First, PNs provided less smokers than expected, leading to a longer inclusion period and omission of also a 12-month follow-up as stated in our trial register, (NL7020/NTR7218). Yet, a 6-month study follow-up is still an acceptable period for assessing treatment effectiveness (West *et al.*, 2005).

Second, although we aim to include all eligible smoking patients who visit the participating general practices, there is a risk of selection bias by PNs. PNs may tend to invite more smokers who have already shown a willingness to stop smoking or who are deemed to be more easily motivated to participate, as also seen in other studies (Bundy, 2004; de Ruijter *et al.*, 2017a; 2017b). The conversational guidelines found in the intervention’s manual and flowchart handout are aimed to induce PNs to include all types of smokers.

Third, because smokers often just have one face-to-face meeting with a PN and we use mostly online questionnaires at the six months mark, we may face a high attrition rate. This is usual for studies that use online questionnaires (Eysenbach, 2005; Shahab and McEwen, 2009; Webb, 2009). We tried to overcome this by sending additional questionnaire packages so that patients could answer the questionnaire on-site if desired.

In order to try to prevent attrition at the follow-up assessment, we will also provide a shortened questionnaire including three of the aforementioned questions on abstinence (7-day PPA, 24-hour PPA, and 3-month prolonged abstinence) and one question asking the patients about EBSCIs used during their cessation attempt. This shortened questionnaire can be administered via email or telephone.

Lastly, the efficacy of counseling treatment is also dependent on contextual factors such as the patient–counselor relationship (Wampold, 2015). However, due to the nature of this study, targeting the use of evidence-based smoking cessation methods, assessing these contextual factors was beyond the scope of this study.

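### As published, the measure for 3-month prolonged abstinence sets no minimum time since the last quit attempt, so a respondent who quit a week before follow-up would qualify

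*Protocol article*

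**What the plan says.** Under 'Tobacco abstinence', the protocol article sets 7-day PPA at six months as primary and adds: "Secondary outcomes are 24-hour PPA and 3-month prolonged abstinence". The same paragraph describes the measurement: "Prolonged abstinence will be assessed by asking patients whether they have refrained from smoking tobacco since their last quit attempt". A tolerance for early slips is attached to that question: "allowing for a two-week grace period during which the participant could smoke one–five cigarettes".

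It gives a reason for not using a six-month version: "follow-up measurement will take place six months after answering the baseline questionnaire irrespective of the date the participant quit smoking". On quit attempts themselves, "patients will be asked whether and how often they have tried to quit smoking (i.e., no cigarette for 24 h) during the intervention period".

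Under 'Potential limitations', a shortened follow-up questionnaire is described. It holds "three of the aforementioned questions on abstinence (7-day PPA, 24-hour PPA, and 3-month prolonged abstinence") and one question on the cessation methods used. 'Data analysis' compares the conditions on the outcome under its three-month name and adds no further condition.

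**The concern.** The name of the outcome promises a duration that the described measure does not establish. Having stayed off tobacco since the last attempt is a statement about that attempt, whether it began five months or five days ago. Without a quit date or a minimum duration, the two cannot be told apart.

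This is the only sustained-abstinence outcome in the trial. If recent quitters count, it comes close to a restatement of point prevalence, and for very recent quitters the grace allowance makes it more lenient than 7-day PPA. Readers of the results would take the reported rate as evidence of lasting cessation.

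**Working it through.** The plan gives no figure to reproduce. The check is to apply the published rule to concrete respondents and then look for anything in the article that would exclude them.

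**Inputs**
- Duration in the name: three months, about 91 days ('Tobacco abstinence').
- Rule: no smoking since the last quit attempt, with a grace allowance of 14 days and one to five cigarettes (same section).
- A quit attempt counts from 24 hours without a cigarette (same section).
- Follow-up is fixed at six months from the baseline questionnaire, whatever the quit date (same section).

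**Respondent A** stopped 7 days before follow-up and has not smoked since. The answer to the question is yes, so A is classed as prolonged abstinent with 7 days of abstinence against about 91 implied by the label.

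**Respondent B** stopped 10 days before follow-up and smoked five cigarettes three days before it. That is day 10 − 3 = 7 of the attempt, inside the 14-day grace period, and five cigarettes are within the allowance. B is classed as prolonged abstinent. B smoked within the last seven days, so B fails 7-day PPA.

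**Does anything exclude A or B?**
- The quit-attempt items ask whether and how often, not when.
- The shortened questionnaire lists three abstinence questions and one on methods used, and no date.
- The referral-aid consultation includes a date: "Fourth, the smoker selects an EBSCI and chooses a cessation date". This is a planned date, belongs to the experimental condition's procedure and is not listed as a study measure. It cannot serve as the quit date for both conditions.
- 'Data analysis' adds no duration condition.

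Nothing listed excludes either respondent.

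**Are late quits plausible?** Yes. The article rules out six-month prolonged abstinence because follow-up happens "irrespective of the date the participant quit smoking". The baseline motivation item also allows for smokers who plan to quit within three months, within six months, later or not at all.

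**How many?** The document does not give the distribution of quit dates, so any count is illustrative.
- Expected abstinent at the planning rates ('Sample size'), assuming 150 per condition: 150 × 0.05 + 150 × 0.15 = 7.5 + 22.5 = 30. These are rates for 7-day PPA, borrowed here for a different outcome.
- If the last quit dates of those abstinent were spread evenly over six months, the share under three months is 3/6 = 0.5, or 30 × 0.5 = 15.
- If quitting clusters early, the share is smaller. An arbitrary 20% to 30% gives 30 × 0.2 = 6 to 30 × 0.3 = 9.

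The definitional result for A and B does not depend on any of these figures.

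**The case against.** The strongest reply is that the article summarises the item and does not reproduce it. Other items are given verbatim, such as the saliva-test question; this one is not. The outcome carries its duration in its name, and the limitations section refers to a question on 3-month prolonged abstinence. A three-month window in the fielded item or its scoring would be compatible with the text. The authors also plainly saw that time since quitting matters, because they dropped the six-month version for that reason. Exact item wording is often left to the full protocol.

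This limits the point but does not remove it. The article does not merely leave the measurement open: it states how prolonged abstinence will be assessed, and that statement does not deliver the named duration. A reader may infer that the trial will certainly count recent quitters, or never measured three-month abstinence. The document does not support that, because the fielded item is not shown.

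Three further parts of the reply stand. The grace-period example follows from the same missing duration and is not a separate defect. The illustrative count of 15 rests on borrowed rates and evenly spread quit dates. In the experimental condition, which supplies 22.5 of the 30 expected quitters, a cessation date is chosen during the consultation, which suggests earlier quitting there. Finally, nothing shows bias between conditions. As far as the article says, both receive the same item, so what is demonstrated concerns the label and the absolute rate.

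**Conclusion.** The concern holds against the definition as published. The name says three months, while the described measure has no minimum time since the last attempt and no listed item supplies one. Followed literally, it classes a one-week quitter as three-month abstinent and lets a quitter of under 14 days qualify while failing 7-day PPA.

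The size cannot be derived from the document. About half of those abstinent would be affected under evenly spread quit dates and fewer under early clustering; neither pattern is documented, so 15 of 30 should not be read as an estimate.

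The scope is one secondary outcome. It would be tempting to extend the point to the trial's main conclusion, but the primary outcome is 7-day PPA, the sample size is built on it, and the cost-effectiveness analysis counts quitters by point prevalence. None of these uses the prolonged-abstinence measure. The change should be made, but it is not critical to the trial's main test.

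**What to change.** What to do depends on what was fielded.

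1. **If the item can still be changed:** in both the full and the shortened follow-up questionnaires, ask how long ago the last quit attempt began, or ask explicitly about the past three months. Score a respondent as 3-month prolonged abstinent only if the attempt began at least three months before follow-up and any smoking since then stayed within the grace allowance, limited to the first two weeks after the quit date. State that the three months run from the quit date, so that about 91 − 14 = 77 days after the grace period must be smoke-free. Respondents who quit more recently count as not prolonged abstinent. Patients with no follow-up are not recoded by this rule; they stay with the planned multiple imputation.
2. **If the fielded item already has a three-month window:** correct the published definition to say so, and state how the grace period counts.
3. **If data were collected without a window or a date:** relabel the outcome as abstinent since last quit attempt, and drop the three-month claim.

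The cost is one extra item, which matters somewhat for a short form meant to limit attrition, plus a sentence of scoring. The quit date will be recalled and therefore imprecise; a direct three-month question avoids asking for a date. The reported rate will be lower.

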#### Smoking cessation method chosen

Patients will be asked which EBSCIs they have used in any previous smoking cessation attempts and to grade the methods they have used on a scale ranging from 1 = very bad to 10 = very good. The following EBSCIs constitute the response options: face-to-face counseling, eHealth, telephone counseling, group counseling, pharmacotherapy, and nicotine replacement therapy. If a participant uses a smoking cessation method that is not included in the response options, it will be possible to indicate this by entering a free text. The smoking cessation method selected will be assessed at a 6-month follow-up.

#### Quality of life and healthcare costs

Quality of life measures EuroQol (Janssen *et al.*, 2013) and ICECAP (Al-Janabi *et al.*, 2012) will be used to measure the incremental costs per quality-adjusted life year (QALY). Healthcare costs (e.g., productivity losses, medical consumption, and consumption of informal care) will be measured via the iMTA Medical Consumption Questionnaire [iMCQ (Bouwmans *et al.*, 2015]. The valuation of costs will be based on the latest Dutch standards, which include, for example, hourly wage of HCPs and standardized costs for consults in the GP setting (Tan *et al.*, 2012; Hakkaart-van Roijen *et al.*, 2015). Quality of life and healthcare costs will be assessed both at baseline and at 6-month follow-up.

#### Informed decision-making

Decisional conflict (e.g., ‘I feel I have made an informed choice’) will be assessed via 16 items on a 5-point Likert scale (1 = strongly disagree; 5 = strongly agree) (O’Connor, 1995; 2010). Decisional conflict will be assessed at a 6-month follow-up.

#### Contact between PN and smoker

The contact between the PN and the smoker will be evaluated because a constructive and empathic relationship between PN and smoker is an important factor for intervention success (Rogers, 2003). First, patients have to indicate which topics have been discussed during the guidance and referral advice (e.g., ‘He/she (the PN) has asked you how motivated you are to stop smoking’); (0 = yes; 1 = no). Second, the relationship between smoker and PN will be assessed via six items (e.g., During a conversation about quitting smoking, I have the feeling that my caregiver is offering me choices’) on a 5-point Likert scale (1 = strongly disagree; 5 = strongly agree). The contact between the PN and the smoker will be assessed both at baseline and at 6-month follow-up.

#### Appreciation of the intervention

After assessing which intervention materials have been noticed by the patients (e.g., ‘Have you seen the intervention’s poster in the waiting room of your general practice?’); (0 = yes; 1 = no), appreciation of the materials (e.g., ‘I think the StopWijzer materials are understandable’) will be assessed via four 5-point Likert items (1 = strongly disagree; 5 = strongly agree). Moreover, patients will be asked to grade the intervention materials (1 = very bad; 10 = very good) and patients and for comments and suggestions entering free text. The appreciation of the intervention will be assessed at a 6-month follow-up.

#### Demographics, smoking characteristics, health status, and health literacy

Demographics will be assessed via age, gender (0 = male; 1 = female), nationality (0 = other nationality; 1 = Dutch nationality), education level (1 = low: no education, primary, or basic vocational school; 2 = medium: secondary vocational school or high school; 3 = high: higher vocational school or university), and occupation of the principal wage earner of the household.

Motivation to quit smoking (e.g., Bolman *et al.*, 2002; Mudde *et al.*, 2006) will be assessed via four items. Three items (e.g., ‘I am planning to quit smoking’) use 7-point Likert scales (1 = certainly not;7 = certainly yes). One item assesses whether smokers want to quit smoking including the time frame (1 = yes, within one month; 2 = yes, within three months; 3 = yes, within six months; 4 = yes, within one year; 5 = yes, but not within one year; and 6 = no, I do not plan to quit smoking).

The intention to use a specific smoking cessation method will be assessed via 20 items (e.g., ‘In order to stop smoking, I can best make use of nicotine replacement therapy’). All items use be 7-point Likert items (1 = certainly not to 7 = certainly yes). The questions were developed for this study based on the I-Change model, which aims at explaining motivational and behavioral change via integrating various social cognitive theories (De Vries, 2017).

The current use of e-cigarettes will be assessed via one item (‘Do you use e-cigarettes?’; 1 = no; 2 = yes, without nicotine; 3 = yes, with nicotine).

Cigarette dependence will be assessed via the Fagerström Test for Cigarette Dependence (Heatherton *et al.*, 1991; Fagerström, 2011). The six items of the scale will be converted into an overall score ranging from 0 to 10. The dependence level is classified as 0–2 = low; 3–4 = moderate; 5–6 = strong; and 7–10 = very strong.

The health status of the smoker (e.g., ‘Do you have type 2 diabetes?’) will be assessed for six diseases (0=‘yes’; 1=‘no’): COPD, cancer, type 2 diabetes, cardiovascular diseases, asthma, and depression (Bouwmans, 2018).

Health literacy (e.g., ‘How often do you get help with reading letters or folders of your GP, the hospital or other health care services?’) will be assessed via three items (1 = never; 5 = always) (Chew *et al.*, 2004). All variables described in this paragraph will be assessed at baseline.

